**Fig. 1 Fig1:**
[figure not shown]
Flowchart of the composition of the target population from which the study population will be sampled

In-care and not-in-care participants were recruited consecutively, to avoid duplicate recruitment attempts. The recruitment period of the in-care group, and the LZA-cohort in parallel, was December 2017–January 2021. Recruitment of participants in the not-in-care group was executed between January 2021 and January 2022. At baseline, participants were interviewed about their functioning with respect to important aspects of life (see instruments) by a pool of trained interviewers. All participants will receive a financial compensation of €15, for each interview. Interview data will be matched with information retrieved from patient files that concerns important aspects of the care process. Follow-up interviews will be held two years after the first interview and will consist of the same set of instruments as administered during interview 1. The recruitment period of follow-up interviews of the in-care cohort and the LZA-cohort will start in December 2019 to end in June 2022. Not-in-care participants will be approached to participate in interview 2 between January and September 2023.

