**Methods:**

A cohort design will be used. A representative sample of community-dwelling adults with an SMI, including those in care (*n* = 650) and not in care (*n* = 150), will be followed over time. During a two-year time period, participants will be interviewed twice using a wide-ranging set of validated instruments. Interview data will be matched with administrative data about the care process, as retrieved from their patient files. Primary outcomes are changes over time in recovery, societal participation and quality of life, controlled for the occurrence of adverse life-events during follow-up. Additionally, prevalence estimates of and associations between social functioning, safety and discrimination, substance use and health indicators will be investigated.

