## Methods

### Study design

The Deinstitutionalization Amsterdam Client-study is a cohort study that started in December 2017. The study is planned to include approximately 800 adults with an SMI. The study population is designed to be representative for the target population of community-dwelling adults with an SMI at the city level, the level of the city-districts and the level of the city’s quarters (i.e. combined neighborhoods). To acquire a better insight into developments in the functioning and recovery of community-dwelling adults with an SMI and their associated needs for care/support, a comprehensive set of measurement instruments will be administered twice, with a two-year time interval, by means of semi-structured interviews. Also, the occurrence of adverse life-events during follow-up will be associated with developments in people’s functioning (i.e. social recovery and societal participation) over the course of time. Additionally, information about the care processes during that time will be retrieved from participants’ patient files.

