Research question 3 will be analyzed using data from the baseline and follow-up measurement by means of generalized linear mixed models with repeated measurements of recovery, quality of life and societal participation as dependent variables. The time between both measures will be included as a within-subjects factor. The same set of predictor variables as mentioned above will be treated as time-dependent independent variables. Additionally, the total score on Brugha’s life-events questionnaire will be included as a potential mediator to assess the effect of having experienced adverse life-events in the time period between baseline and follow-up on the associations between predictor and outcome variables. All variables will be checked for potential outliers. Missing values will be dealt with appropriately. Participants with > 80% missing values on all items will be deleted from the final dataset. For most measures, descriptive analyses will be carried out and the proportion of missing values will be reported for each variable of interest. In subsequent statistical analyses, values missing at (completely) random (i.e. MAR and MCAR) will be deleted pair wise. Values that are not missing at random (NMAR) will be imputed with either the mean, median or using multiple imputation, whichever is most appropriate. Concerning outcome measures that are a sum score of items, instructions from the instrument developers will be followed (e.g., impute missing values with the mean value of the non-missing items and calculate a sum score only if < 10% of items are missing).

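### The follow-up windows close about 17 and 20 months after recruitment ends, so the stated two-year interval cannot hold for late recruits

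*Protocol article*

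**What the plan says.** **Interval.** The Study design section says that the instruments "will be administered twice, with a two-year time interval". The Participants section (text after Figure 1) repeats this: "Follow-up interviews will be held two years after the first interview". Neither place gives a tolerance around two years.

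**Baseline dates (Participants).** "The recruitment period of the in-care group, and the LZA-cohort in parallel, was December 2017–January 2021". For the other cohort: "Recruitment of participants in the not-in-care group was executed between January 2021 and January 2022".

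**Follow-up dates (same paragraph).** "The recruitment period of follow-up interviews of the in-care cohort and the LZA-cohort will start in December 2019 to end in June 2022". For the other cohort: "Not-in-care participants will be approached to participate in interview 2 between January and September 2023".

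**Size and use.** The abstract plans a sample "including those in care (*n* = 650) and not in care (*n* = 150), will be followed over time" and defines the primary outcomes as changes over time in recovery, societal participation and quality of life. For the repeated-measures models, the Statistical methods section says: "The time between both measures will be included as a within-subjects factor".

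**The concern.** Both windows open exactly 24 months after recruitment opened (December 2017 to December 2019, and January 2021 to January 2023), so the dates themselves treat 24 months as the interval. The closing dates do not follow the same rule in either cohort. People recruited in the last months of each period reach two years only after the window has closed.

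Every primary outcome is a change between two interviews, so both the timing and the existence of interview 2 matter. A shortened interval would fall only on the latest recruits, and the two cohorts have different shortest intervals. Interval length is therefore tied to calendar period and to cohort. Incidence during follow-up (research question 5) and the analysis of life events between the two interviews also depend on how long follow-up lasts.

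**Working it through.** **Inputs.** The dates are those in the Participants section and the interval is 24 months. Planned sizes are 650 in care and 150 not in care (abstract). Cohort estimates of 1739, 820 and 157, with response rates of 33%, 20% and 50%, come from the Participants section.

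**1. The plan's own sample size.** 1739 × 0.33 + 820 × 0.20 + 157 × 0.50 = 573.9 + 164.0 + 78.5 = 816, in line with the stated figure of approximately 800. In-care plus LZA is 573.9 + 78.5 = 652, which matches 650, so the 650 appears to include the LZA cohort. Not-in-care is 164 against 150 stated. The stated 650 and 150 are used below.

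**2. Late recruitment months.** A month is late if that month plus 24 falls after the last month of the follow-up window.

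| | In-care and LZA | Not-in-care |
|---|---|---|
| Recruitment | Dec 2017 to Jan 2021: 38 months | Jan 2021 to Jan 2022: 13 months |
| Window closes | June 2022 | Sept 2023 |
| Last month that reaches 24 months in time | June 2020 | Sept 2021 |
| Late months | July 2020 to Jan 2021: 7 | Oct 2021 to Jan 2022: 4 |
| End of recruitment to close of window | about 17 months | about 20 months |
| Close needed for 24 months | Jan 2023 (7 months later) | Jan 2024 (4 months later) |

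**3. Share affected, with even accrual and a strict 24 months.**
- In-care and LZA: 7/38 = 18.4%; 650 × 7/38 = 120.
- Not-in-care: 4/13 = 30.8%; 150 × 4/13 = 46.
- Together: 166/800 = 20.7%. Counting in days, with different start and end days within the stated months, gives 18.9% to 20.9%.

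**4. If accrual was not even.** Let the late months accrue at r times the earlier rate. The shares are then 7r/(31 + 7r) and 4r/(9 + 4r), weighted by 650 and 150.

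| r | 0.25 | 0.5 | 1 | 1.5 | 2 |
|---|---|---|---|---|---|
| Share of 800 | 6.2% | 11.7% | 20.7% | 28.1% | 34.1% |

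**5. If earlier interviews count as two-year (even accrual).**
- Up to 3 months early: 4/38 and 1/13 remain late; 68.4 + 11.5 = 80, or 10.0% of 800.
- Up to 6 months early: 1/38 and 0/13; 17 people, or 2.1%.
- Up to 7 months early: none.

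**The case against.** - **The windows need not be last-interview dates.** One is worded as a recruitment period for follow-up interviews, the other as the time when people are approached. At baseline, the section on recruitment at Arkin separates approach from interview and re-books some missed appointments several weeks later. This stands in part: 17 and 20 months are approximate. A lag of weeks does not plausibly cover 7 months, and is unlikely to cover 4.
- **A reader might infer that one in five participants cannot have interview 2, or will be lost.** The article does not support this. Nothing in it says that late recruits are dropped. On the stated dates they can still be interviewed at about 17 to 24 months (in-care and LZA) or 20 to 24 months (not-in-care), so change can still be measured. The one-in-five figure also needs even accrual and zero tolerance, and the article states neither.
- **A reader might infer that the model treats a 17-month and a 24-month change alike.** The sentence is ambiguous. A within-subjects factor suggests two waves, but time between measures can equally mean elapsed time, in which case part of the remedy is already planned.
- **An article condenses the full protocol, and visit tolerances may be given there.** This is fair, and the missing tolerance is not the finding. The finding is that an interval and a set of dates, both stated, disagree.
- **Much of the planned output is descriptive or uses baseline data only.** This stands, and confines the point to the longitudinal analyses.

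**Conclusion.** The contradiction holds in both cohorts, and nothing in the article resolves it. For the last recruits, the stated windows fall up to 7 months (in-care and LZA) and up to 4 months (not-in-care) short of the stated two years.

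The number of people affected is conditional. It is about 166 of 800 (21%) with even accrual and a strict 24 months, about 6% to 34% over the accrual patterns tried, and about 10% with a three-month tolerance. No one would be affected only if interviews 7 months early counted as two-year interviews.

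The supported consequence is shorter, uneven intervals for a minority, tied to calendar period and cohort, with some missed interviews possible but not shown. Because the primary outcomes are changes over time, this should be settled before the longitudinal analysis.

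**What to change.** 1. **Reconcile the dates with the interval**, in one of two ways.
   - Restate the interval as about 17 to 24 months (in-care and LZA) and about 20 to 24 months (not-in-care). This needs no extra fieldwork; the price is a less tidy stated interval.
   - If fieldwork capacity allows, extend the windows to January 2023 and January 2024. This costs more. The article schedules no interviews between June 2022 and January 2023, January 2024 lies beyond all stated fieldwork, and nothing in it shows that interviewers would be available.
2. **In either case, make the time variable explicit in Statistical methods.** State that the actual number of months between a participant's two interviews enters the mixed models as a continuous variable.
3. **Add a sensitivity analysis** limited to participants interviewed close to 24 months, with the band fixed in advance.
4. **Replace the assumed share with a count.** Baseline recruitment is reported as complete, so the sponsor can report from its own interview dates how many people fall in the late months, and the distribution of intervals by cohort.

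Items 2 to 4 cost slight extra analysis.

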### Recruitment

#### Recruitment in-care cohort at Arkin

Within Arkin, several teams are selected from which patients with an SMI will be asked to participate. The teams included are Flexible Assertive Community Treatment teams (FACT), basic mental health care teams (BMHC) with a focus on more stable patients with a chronic mental health problem, forensic FACT-teams of the Forensic Ambulatory Care (FAC) and “Jellinek” Outreaching Teams (JOT) for substance dependency [46]. FACT-teams provide multidisciplinary ambulatory care for the treatment and guidance of people with an SMI. BMHC-teams provide general ambulatory treatment that involves long-term guidance with respect to relapse-prevention, monitoring and care-coordination for stabilized and low-complexity chronic psychiatric patients at low risk of psychiatric crisis. The target population of FAC is primarily a forensic population. FAC-teams offer both voluntary and involuntary treatment. FAC-patients are typically diagnosed with psychiatric, addiction and/or personality disorder(s) and multi-problem situations (that include social and judicial problems). FAC-teams provide ambulatory outreaching care and outpatient treatment. JOT-teams target people with functioning impairments that result from severe addiction problems and (often) comorbid disorders. JOT provides ambulatory multidisciplinary care.

Participants are selected at their location of care. Primary caregivers (i.e. case managers or psychiatrists) will assess and advise about eligibility for participation and a preferred approach-strategy. When direct approach is advised, a research assistant will contact these patients to inform them about the study and to invite them for participation. Caregivers that prefer to first inform their patients themselves will hand out a folder and inform their patient during the next consult. Only patients who wish to participate will be contacted by a research assistant to schedule an interview appointment. Patients who temporarily meet an exclusion criterion will be re-approached at a more suitable time, as advised by their caregiver. Interviews will be conducted at the location of care, an interview cubicle at the Public Health Service Amsterdam or, if possible, at home. Informed consent is given prior to the start of the interview. In case of no-shows without an explicit wish to withdraw from the study, patients will be approached for a new appointment. In case of no-show due to sickness or mental instability, a new appointment will be scheduled several weeks into the future.

#### Recruitment in-care cohort at GGZ inGeest

GGZ inGeest will recruit participants at several of their mental health care departments. These are selected on the basis of their distinct care facilities and specific types of treatments that are commonly provided to people with an SMI. Patients from regular FACT-teams will be selected as potential participants. Additionally, participants will be selected at mental health care outpatient clinics whose patients are either stabilized with respect to medication use and crisis management or who receive specialized care for distinct psychiatric diagnoses (e.g., bipolar disorder).

After the research assistant has given an oral presentation of the study, primary caregivers will be asked to select and recruit patients eligible to participate. Patients who wish to participate can inform their caregiver and will be approached by telephone by a research assistant. Further explanation of participating in the study will be provided by sending an information brochure by mail. Then, participants will be contacted to schedule an interview appointment.

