With respect to the in-care and not-in-care cohorts, their relative proportions within the total SMI-population in Amsterdam are approximately 76 and 24%, respectively [30]. Furthermore, around 90% of both groups lives independently (i.e. community dwelling). In-care participants will be recruited at the two largest mental health care providers in Amsterdam, Arkin and GGZ inGeest. Together, these organizations are estimated to provide care/treatment to two thirds of the total in-care population of people with an SMI in Amsterdam [39]. The remaining 33% of the in-care SMI-population, those who receive mental health care from one of several other (small) providers, will not be included as we expect to obtain a representative sample of the in-care population from the selected service providers. Moreover, recruiting participants at numerous care providers would require a disproportional effort and is therefore considered unfeasible. The ‘not-in-care’ participants will be recruited at a variety of social welfare and social support organizations in Amsterdam, including organizations that target the homeless (e.g., HVO-Querido, Leger des Heils, Cordaan, Volksbond). In this group, the SMI-criteria will be assessed during the interview.

As such, on the basis of 1) the assumed average SMI prevalence of 1.6% among the adult population of the selected quarters (237,157 * 1,6% = 3795 people), and 2) the proportion of adults with an SMI who are registered as a mental health care patient (76%, *n* = 2884), and 3) of whom at one of the two main mental health care providers in the city (66%, *n* = 1903) and 4) the proportion within this group who live independently (i.e. community dwelling) (90%), the in-care cohort is estimated to consist of 1739 adults with an SMI. On the basis of the aforementioned proportions, the not-in-care cohort is estimated to consist of 820 people. The LZA-cohort potentially consists of 157 former LZA-participants who gave permission to be re-approached. Based on expected response rates of 33% in the in-care cohort, 20% in the not-in-care cohort and 50% in the LZA-cohort, the study sample will consist of approximately 800 participants. Figure 1 presents a flowchart depicting the composition of the study population.

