### Bias

Some types of bias will need to be taken into account when interpreting the results.

We set out to include at least 30% of the population with an SMI living within the selected quarters in the city of Amsterdam, recruited from the two main mental health service providers and several primary care- and social support services. Both the selection of quarters and the recruitment method, can introduce selection bias. Although we only include about 8% of the estimated total SMI-population in Amsterdam, we assume that in spreading the selected quarters over the seven residential city districts and recruiting within the two most populated quarters within those districts, we include a representative sample of the SMI-population in Amsterdam. In addition, it is unlikely that the population in other (smaller) quarters differs systemically from the population in the selected quarters on the background- and outcome measures of this study: social-economical and background characteristics of the general population do not vary widely within quarters (in contrast to variance between quarters). As the SMI-population moves within the same (social) housing pool as the general population, selection bias due to sampling in specific quarters is expected to be limited.

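### Provider is in none of the listed models, although Arkin and GGZ inGeest recruit by partly different routes and from partly different teams, and the recruitment-method bias that the plan names is left unaddressed

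*Protocol article*

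**What the plan says.** **Arkin** (Recruitment in-care cohort at Arkin). Primary caregivers "will assess and advise about eligibility for participation and a preferred approach-strategy". Two routes follow. One is direct: "When direct approach is advised, a research assistant will contact these patients to inform them about the study and to invite them for participation". The other goes through the caregiver: "Caregivers that prefer to first inform their patients themselves will hand out a folder and inform their patient during the next consult". On the second route only patients who want to take part are contacted. Re-approach is foreseen: "Patients who temporarily meet an exclusion criterion will be re-approached at a more suitable time, as advised by their caregiver". The teams are FACT, basic mental health care for more stable chronic patients, forensic ambulatory care, and addiction outreach.

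**GGZ inGeest** (Recruitment in-care cohort at GGZ inGeest). After a presentation of the study, "primary caregivers will be asked to select and recruit patients eligible to participate". Interested patients tell their caregiver and are then telephoned. No direct-approach route is described. The teams are regular FACT teams and outpatient clinics, the latter for stabilised patients or for specific diagnoses.

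**Representativeness** (text on the cohorts under Exclusion criteria). The remaining, smaller providers are left out because "we expect to obtain a representative sample of the in-care population from the selected service providers".

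**Bias.** The section states: "Both the selection of quarters and the recruitment method, can introduce selection bias". The argument after that sentence deals with the choice of quarters.

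**Statistical methods.** The baseline regressions use unmet needs, discrimination, stigma and victimization as predictors. Age, sex, BPRS-E, AUDIT/DUDIT, RAND SF-36 and city-district are added as covariates. The mixed models reuse the predictors and add the life-events score. Neither list contains provider, team or recruitment route.

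**The concern.** Provider is tied to who gets into the sample and to what kind of patient is available to be sampled. If the providers differ both on a predictor (stigma, unmet need, victimization) and on an outcome (recovery, participation, quality of life), a pooled regression without provider reads part of that difference as an association between predictor and outcome. The article fixes a covariate list that adjusts for city-district and leaves out the factor along which recruitment differed.

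The descriptive results are exposed in another way. Research questions 4 and 5 cover compliance, therapeutic alliance, crises, compulsory treatment and victimization, and are answered at least partly by proportions, which no regression covariate protects. Where the caregiver selects, one party to the therapeutic alliance influences who is measured on it. The forensic teams, named only at Arkin, also give involuntary treatment, so the provider mix bears on the compulsory-treatment estimate.

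**Working it through.** **1. The plan's own figures.** The text on the cohorts gives cohort sizes of 1739 (in care), 820 (not in care) and 157 (LZA), with expected response rates of 33%, 20% and 50%.

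- In care: 1739 × 0.33 = 573.9, about 574
- Not in care: 820 × 0.20 = 164
- LZA: 157 × 0.50 = 78.5
- Total: about 816, consistent with the stated figure of approximately 800

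The article gives no split by provider and no provider-specific response rate. Everything numerical below is therefore illustration on assumed inputs.

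**2. The two recruitment descriptions compared.**

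| Step | Arkin | GGZ inGeest |
|---|---|---|
| Caregiver screens first | yes | yes |
| Caregiver informs, willing patients contacted | yes, one of two routes | yes, the only route described |
| Research assistant approaches directly | yes, if the caregiver advises it | not described |
| Re-approach after temporary exclusion | yes, on caregiver advice | not mentioned |
| FACT teams | yes | yes |
| Stabilised patients | yes | yes |
| Forensic and addiction outreach teams | named | not named |
| Diagnosis-specific clinics | not named | named |

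The difference is real but partial.

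**3. Confounding of an association (the part a provider factor addresses).** Assume two providers with sample shares p and 1 − p, no association within provider, and provider differences d on both predictor and outcome, in within-provider SD units. The pooled correlation is p(1 − p)d² / (1 + p(1 − p)d²).

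- p = 0.5, d = 0.2: 0.25 × 0.04 / 1.01 = 0.010
- p = 0.5, d = 0.5: 0.25 × 0.25 / 1.0625 = 0.059
- p = 0.7, d = 0.5: 0.21 × 0.25 / 1.0525 = 0.050

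The spurious correlation is about 0.01 to 0.06 before adjustment. The standard error of a correlation near zero is about 1/√574 = 0.042. BPRS-E, AUDIT/DUDIT and RAND SF-36 would remove part of this.

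**4. Distortion of the provider mix.** Let s be one provider's true share and r the ratio of its response rate to the other's. Its sample share is sr/(sr + 1 − s).

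- s = 0.5, r = 1.5: 0.60, a shift of 10 points
- s = 0.5, r = 3: 0.75, a shift of 25 points
- s = 0.7, r = 1.5: 0.778, a shift of 8 points
- s = 0.7, r = 3: 0.875, a shift of 17.5 points

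If provider means differ by 0.2 to 0.5 SD, the bias in the in-care mean runs from 0.2 × 0.078 = 0.016 SD to 0.5 × 0.25 = 0.125 SD.

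**5. Selection within a provider.** At 33% response, a difference d between participants and non-participants biases the mean by 0.67d. For d = 0.1 to 0.5 SD this is 0.07 to 0.34 SD, against a standard error of 0.042 SD. This component can be the largest, and a provider factor does not touch it.

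**The case against.** The case against has five parts.

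- **The contrast can be drawn too sharply.** A reader might infer that GGZ inGeest hand-picks while Arkin samples openly. The article does not support that: Arkin caregivers also screen, and they may choose an opt-in route like the one at GGZ inGeest. Re-approach at Arkin depends on caregiver advice, and silence about it at GGZ inGeest may only reflect a condensed article. What stands is that direct approach is described at one provider only.
- **Different teams are not a defect.** Forensic and addiction teams broaden coverage, and the planned scores capture part of the case mix. This is right as far as it goes. Those scores do not measure recruitment route or all case-mix differences.
- **The Bias section is candid.** It lists the recruitment method openly, and its conclusion of limited bias covers only sampling by quarter. It would be wrong to say that the plan declares recruitment bias limited. The gap is that the named source gets no discussion while a representative in-care sample is still expected.
- **The 33% response rate has a denominator.** It is applied to the estimated 1739 people, so a claim that the planning figure has no denominator fails.
- **Details belong to a full protocol or SAP.** Weighting and response reporting may well be there, and their absence here is no finding. The covariate list is different, because the article states it and it omits provider.

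**Conclusion.** The point holds as an omission in the stated models and an unfinished bias argument. Provider belongs in the adjustment set, because recruitment route and team mix partly differ by provider and the listed covariates capture that only in part. The Bias section needs to deal with the second source of bias that it names.

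The size cannot be derived from the document. On the assumed ranges, confounding through provider is at most modest: a correlation of up to about 0.06 before adjustment, and up to about 0.13 SD in a mean through a distorted mix. Selection within providers could be larger, and no provider term removes it.

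A reader might also infer a definite prevalence bias. With an assumed true victimization prevalence of 30%, 20% among caregiver-selected patients, and 30 to 50% of the sample from GGZ inGeest, the estimate falls by 0.10 × 0.30 to 0.10 × 0.50, that is 3 to 5 points. The 95% half-width is 1.96 × √(0.3 × 0.7/574) = 3.7 points. The documents do not support this as a finding: none of the three inputs comes from the article, and the calculation assumes no selection at Arkin, where caregivers also screen.

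**What to change.** - **Models.** Add a recruitment-source factor (Arkin / GGZ inGeest, with not-in-care as its own level where cohorts are pooled) to the baseline regressions and the mixed models.
- **Description.** Report the in-care prevalence estimates by provider and, where numbers allow, by team type.
- **Text.** In the paragraph that expects a representative in-care sample and in the Bias section, state that caregiver selection may favour some patients. State also that the provider factor adjusts associations only and leaves selection within a provider in place.
- **Comparison.** If the providers can supply aggregate caseload data on patients who meet the SMI criteria, compare participants with that caseload. Counts by age and postal code alone would not do, because they ignore the SMI criteria. Handle LZA participants separately, since the location criterion does not apply to them. Weighting is optional.

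The cost is small. Provider should be known for in-care participants, because their files are retrieved from Arkin or GGZ inGeest. The factor uses one or two degrees of freedom. Stratum estimates are less precise: with an assumed even split (287 each) and 30% prevalence, the half-width is 1.96 × √(0.21/287) = 5.3 points instead of 3.7. The caseload comparison takes more work, as it must be reconstructed over the recruitment period. Baseline in-care recruitment ended in January 2021, so only analysis and reporting can still change.
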